### Baseline assessments

#### Anthropometric evaluation

Anthropometric evaluation will be performed by the same evaluator and will include weight, height, arm circumference, tricipital skinfold, and adductor pollicis muscle thickness. Subsequently, the body mass index will be calculated according to the Quetelet equation and the arm muscle area will be corrected using the formula proposed by Frisancho [23, 24].

For anthropometric measurements, the following equipment will be used: weight scale (Relaxmedic Your Way), portable stadiometer (InLab), inelastic and inextensible measuring tape with values in centimeters, and an adipometer (Lange®; Cambridge Scientific Industries, Watertown, MA, USA). Anthropometric assessments will be performed on both the affected and unaffected sides of the body.

The thickness of the rectus femoris and biceps brachii muscles, both affected and unaffected by the stroke, will be measured with a BodyMetrix BX-2000 A mode ultrasound device (Intelametrix, Livermore, CA, USA) with a 2.5-MHz transducer. Each location will be measured two or three times, based on the software’s compliance with these measurements, and the average will be used to represent the final thickness [25].

#### Body composition assessment

Multifrequency electric bioimpedance will be performed with the SECA mBCA525 body composition analyzer, with the patients in a supine position, with their legs apart, hands open, palms down, and separated from the body. Eight tetrapolar electrodes will be connected to assess the impedance of the trunk, arms, and legs at six different frequencies (1, 5, 50, 250, 500, and 1000 kHz).

#### Muscle strength assessment

Handgrip strength will be measured using a hydraulic hand dynamometer (Saehan Hydraulic Hand Dynamometer®, Model SH5001, Saehan Corporation, Korea), which measures the force produced by an isometric contraction applied to the handles, and the value will be recorded in kilogram force. Three measurements will be performed and the maximal value achieved will be recorded with a 15-s rest interval between measurements on the affected and unaffected sides [26].

Lower limb strength will be assessed according to the 30-s chair stand test using a chair placed against a wall; the test begins with the patient sitting in the chair, with their back straight, feet aligned with the shoulders, and the arms crossed at the wrists and held against the chest. At the “go” signal, the patient will stand up straight and then return to the initial seated position. The number of correctly executed cycles within 30 s will be counted, and the incorrect cycles will be discarded [27].

The NIHSS item 6 score will be used to verify lower limb strength. The patient will be placed in a supine position with the evaluated leg extended to 30°, and we will assess whether the limb falls within 5 s. Each limb is tested in turn, beginning with the nonparetic leg. The examiner will only record the score as untestable in cases of amputation or joint fusion at the hip. This item is scored as follows: 0 = no drift, the leg is held in the 30-degree position for the full 5 s; 1 = drift, the leg falls before the end of the 5-s period but does not touch the bed; 2 = some effort against gravity, the leg falls to the bed before 5 s although there is some effort made against gravity; 3 = no effort against gravity, the leg falls to the bed immediately; 4 = no movement; and UN = untestable owing to amputation or joint fusion at the hip [28].

#### Functional capacity assessment

The mRs will be applied, with scores ranging from 0 to 6; the higher the value, the greater the degree of disability. Death is classified as a score of 6 [21].

The Timed Up and Go test will assess mobility and balance by measuring the time it takes the patient to get up from a chair, walk in a straight line for 3 m (at a comfortable and safe pace), turn around, walk back, and return to a seated position on the chair [29].

#### Dependence degree assessment

The Barthel Index will be used to measure functional independence and mobility in chronically ill patients. The scale consists of 15 items, with scores ranging from 0 to 100 (0–20 indicating total dependence; 21–60 severe dependence; 61–90 moderate dependence; 91–99 light dependence, and 100 independence) [21].

#### Quality of life assessment

The EuroQol-5D will be used to assess the individuals’ perceptions of quality of life through five domains of mobility, personal care, usual activities, pain/discomfort, and anxiety/depression; the higher the value, the worse the quality of life perception. At the end of the questionnaire, the patient must indicate their health status using an ordinal scale from 0 to 100; the closer to 0 the worse their health status and the closer to 100 the better their health status [17].

#### Assessment of anxiety and depression

The Hospital Anxiety and Depression Scale will be used to screen for anxiety and depression and assess the severity of mood disorders [30].

#### Biochemical dosages

In the first 24 h after stroke and on the 7th hospitalization day, the patient will have blood samples collected for the analysis of insulin and interleukin-6 levels by enzyme-linked immunoassay, in which the amount of protein in the extract will be determined using the Bradford method with the final concentration adjusted to 1 mg/ml. The activity of metalloproteases 2 and 9 will be obtained by zymography as described by Tyagi et al. [31].

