The aim of the study is to verify the effectiveness of creatine supplementation on functional capacity, strength, and changes in muscle mass during hospitalization for stroke compared to usual care. A descriptive and comparative evaluation between groups in order to verify the inflammatory and potential serum biomarkers behavior during hospitalization will be performed with all participants randomized. A follow-up 90 days after stroke to verify functional capacity, muscle strength, mortality, and quality of life will be carried out.

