#### Planned statistical methods

Statistical Considerations Baseline is defined as the randomization visit and the end of the trial is defined as the final visit. Categorical data will be summarized by treatment group, using the number and percentages of subjects.For the calculation of percentages, the denominator will be the number of subjects in the analysis set.Continuous data will be presented using the number of subjects, mean, standard deviation, median, lower quartile, upper quartile, minimum, and maximum. Both the absolute values and the change from baseline will be presented. The treatment group and visit will present descriptive statistics for all endpoints (if applicable). All statistical tests will be carried out as two-sided and performed on a 5 % significance level. Estimated treatment differences and 95% CIs will be presented together with the corresponding *p*-value. All safety endpoints will be presented using descriptive statistics and no formal statistical tests will be applied.The evaluation of continuous variables of the characteristics between the groups will be analyzed by the *t*-test or Mann-Whitney.The assessment of variation of serum levels of biomarkers, muscle mass, and strength between groups and time will be done by the mixed regression models.Kaplan-Meier survival curves will be used to show the survival in the groups within 90 days. Considering day zero as the day of randomization and entering into the study, patients related the final date they had each outcome. This is appropriate as it takes into account what happened during the course of the study. *P*-values were obtained through proportional Cox regression models and a value of 5% was considered statistically significant.All adverse events will be summarized. The summaries will include the number of events, the number of subjects, and the proportion of subjects reporting these events and will be tabulated by system organ class.

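### A protein adjustment to 1 mg/ml is attached to the insulin and interleukin-6 immunoassay, which does not fit the serum levels that the plan sets out to analyse

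*Protocol article*

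**What the plan says.** Under Biochemical dosages, samples are taken in the first 24 h and on the 7th hospital day: "the patient will have blood samples collected for the analysis of insulin and interleukin-6 levels by enzyme-linked immunoassay". The same sentence continues, joined by *in which*, with the protein step: "the amount of protein in the extract will be determined using the Bradford method with the final concentration adjusted to 1 mg/ml". The next sentence turns to a different assay: "The activity of metalloproteases 2 and 9 will be obtained by zymography". It carries no protein-loading statement of its own.

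Elsewhere the biomarkers are described as serum quantities. The aim at the end of the Background, repeated under Outcomes, is to "verify the inflammatory and potential serum biomarkers behavior during hospitalization". The analysis is given under Planned statistical methods: "The assessment of variation of serum levels of biomarkers, muscle mass, and strength between groups and time will be done by the mixed regression models".

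The article describes no extraction. It names no kit, detection limit, expected analyte level or serum protein level. It does not say whether results are multiplied back to a volume of serum or left relative to protein.

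**The concern.** Bringing a sample to a fixed total-protein concentration puts unequal extracts on a common footing. Blood for an immunoassay yields serum or plasma. The quantity the mixed model needs is the amount of analyte per volume of that fluid. Serum also holds far more than 1 mg of protein per ml, so reaching that target means diluting it by its own protein content.

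Two things are at stake if the sentence is followed as it stands. First, low concentrations of interleukin-6 and insulin are diluted further, and some may become unreadable. Second, the dilution factor is the patient's own serum protein at that visit. If it is not undone, the modelled variable is analyte divided by protein, and it moves when either one moves. With 15 patients per group, there is little room for lost readings or added noise.

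**Working it through.** The only figure the article gives is the 1 mg/ml target. It is set, not derived, so there is no plan figure to reproduce. **Every serum protein level, analyte level and assay floor below is an assumption.**

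**Step 1: dilution factor.** Factor = serum total protein / 1 mg/ml.
- 50 mg/ml: 50-fold
- 70 mg/ml: 70-fold
- 90 mg/ml: 90-fold

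A narrower assumption of 60 to 80 mg/ml gives 60- to 80-fold. Either way the factor runs to tens and differs from sample to sample.

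**Step 2: undiluted level needed to be readable.** Level needed = assay floor × factor. The arithmetic is the same for interleukin-6 (pg/ml) and insulin (µIU/ml).

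| Assumed floor | 50-fold | 70-fold | 90-fold |
|---|---|---|---|
| 0.1 | 5 | 7 | 9 |
| 0.5 | 25 | 35 | 45 |
| 1 | 50 | 70 | 90 |
| 2 | 100 | 140 | 180 |

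At 70-fold, interleukin-6 of 10 pg/ml becomes 10/70 = 0.143 and 50 pg/ml becomes 50/70 = 0.714. Insulin of 20 µIU/ml becomes 20/70 = 0.286. A reading of 0.143 clears a floor of 0.1 but not one of 0.5, so the result turns on the kit.

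Each row also shows that the floor, in serum terms, is not common to all patients. With a kit floor of 0.5, it is 25 for a patient at 50 mg/ml and 45 for one at 90 mg/ml.

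**Step 3: effect of leaving the result relative to protein.** With the analyte's concentration in blood unchanged, ratio of day 7 to day 1 = protein on day 1 / protein on day 7.
- 70 to 65 mg/ml: 70/65 = 1.08, an 8% rise
- 70 to 60 mg/ml: 70/60 = 1.17, a 17% rise
- 75 to 60 mg/ml: 75/60 = 1.25, a 25% rise

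A proportional protein change shared by both groups distorts the time effect. On a log scale it cancels from the between-group difference in change. A change that differs between groups, by chance or otherwise, goes into that difference. Variation between patients adds noise in either case.

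**The case against.** The strongest reply is that this may be a misplaced clause in a condensed article. The wording suits an extract, the next sentence concerns zymography, and kit dilution and reporting unit are ordinarily laboratory-manual detail. Part of this stands: the article does not show that the laboratory will dilute serum in this way. But the step and its target are stated, and the grammar ties them to the immunoassay. That is a written instruction at odds with the stated analysis, not a detail left out.

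A reader might infer more than the text supports:

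- **That much of the inflammatory comparison will fall below detection.** This needs analyte levels and floors the article does not give. With an assumed floor of 0.1 pg/ml, interleukin-6 is readable from 5 to 9 pg/ml; with a floor of 2 pg/ml, 100 to 180 pg/ml is needed.
- **That the adjustment certainly comes before the immunoassay.** The order is a natural reading but is not stated.
- **That the result can no longer be a concentration in blood.** If the dilution is recorded, the reading can be multiplied back, and the words *serum levels* in the analysis section suggest a per-volume result. Back-multiplication does not, however, recover a value that fell below the floor.
- **That the step belongs to the zymography.** This is plausible, but nothing in the article establishes it.

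The scope is also narrow. The metalloproteases are measured by another method and are not reached by this point. The Abstract calls the inflammatory work exploratory, and Outcomes lists it apart from the primary outcomes.

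**Conclusion.** The point holds as an inconsistency between the laboratory instruction and the planned analysis. Its existence needs no outside figure: one section prescribes an extract adjusted to 1 mg/ml protein for a blood immunoassay, and the others call for serum biomarkers analysed as serum levels.

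Its size does rest on assumptions. A literal reading with 50 to 90 mg/ml serum protein gives a 50- to 90-fold dilution that varies by patient and visit. Loss of readings is a risk that depends on the kit, not a demonstrated outcome. The 8% to 25% shifts arise only if results stay relative to protein and serum protein falls by the amounts assumed. The consequence is confined to exploratory interleukin-6 and insulin.

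**What to change.** In Biochemical dosages:

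1. Remove the 1 mg/ml adjustment from the insulin and interleukin-6 immunoassay.
2. Name the matrix (serum or plasma), and assay it neat or at the dilution the kit states.
3. Report both analytes per volume of serum or plasma, to match Planned statistical methods.
4. If the Bradford step was meant for another assay, such as the zymography, move it there in so many words.

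This is a change of a sentence or two and calls for no new blood draws. The article says nothing about sample storage or assay timing, and recruitment began in March 2019, so some samples may already have been run. If any were run after adjustment to 1 mg/ml, convert the results with the recorded dilution factor and identify the readings below the floor, since conversion cannot restore those.

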#### Stable isotope tracer analysis

Compound 3-methylhistidine is a product of the breakdown of contractile proteins and is a marker of muscle degeneration. In the first 24 h after stroke, and on the 7th day of hospitalization, the patient will have blood samples collected for residual 3-methylhistidine evaluation. The patient will then receive 50 mL of a solution containing 10 mg of 99.1% pure D3-methylhistidine (Cambridge Isotope Laboratories, Andover, MA, USA). After 18 h, three 10-mL blood samples will be collected at 1-h intervals. Of 30 patients, 10 will be included in the analysis. The samples will be sent to the Centre for Musculoskeletal Aging Research & NIHR Nottingham BRC (Clinical, Metabolic, and Molecular Physiology research group, University of Nottingham, Royal Derby Hospital Centre, Derby, UK). The ratio between labeled and unlabeled 3-methylhistidine will be evaluated using liquid chromatography-mass spectrometry [32–34].

### Statistical analysis

The Full Analysis Set (FAS) will comprise all randomized subjects who have received at least one dose of creatine. The subjects will contribute to the analysis as randomized. The FAS will be used for efficacy analysis instead of intention-to-treat analysis.

The Per-Protocol (PP) population will comprise all subjects in the FAS who do not have any major protocol deviations (including but not limited to violation of inclusion and exclusion criteria), and who have at least good compliance as reported in the eCRF and for whom the primary endpoint can be derived. The PP will be used for the analysis of the primary endpoint.

The Safety Analysis Set will comprise all subjects who have received at least one dose of creatine or placebo. The subjects will contribute to the analysis as actually treated. The Safety Analysis Set will be used for the evaluation of safety endpoints and the primary endpoint.

Missing values will be treated mathematically by multiple imputation.

All data will be analyzed using Stata SE version 15.0 (StataCorp LLC., College Station, TX, USA).

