#### Sensitivity analysis

The primary analysis will be repeated using the PP and safety analysis set. We will perform analysis using only patients with specific symptoms to each symptoms.

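### As worded, the Full Analysis Set admits only patients dosed with creatine, so it and the per-protocol set drawn from it contain no controls treated as assigned

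*Protocol article*

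**What the plan says.** The Statistical analysis section of the protocol article defines three sets.

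- **Full Analysis Set (FAS).** "The Full Analysis Set (FAS) will comprise all randomized subjects who have received at least one dose of creatine". On grouping: "The subjects will contribute to the analysis as randomized". On use: "The FAS will be used for efficacy analysis instead of intention-to-treat analysis".
- **Per-protocol (PP) set.** "The Per-Protocol (PP) population will comprise all subjects in the FAS who do not have any major protocol deviations", with further conditions on compliance and on the primary endpoint being derivable. On use: "The PP will be used for the analysis of the primary endpoint".
- **Safety Analysis Set.** "The Safety Analysis Set will comprise all subjects who have received at least one dose of creatine or placebo". Its patients are grouped by the product they actually took. On use: "The Safety Analysis Set will be used for the evaluation of safety endpoints and the primary endpoint".

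The Sensitivity analysis section adds: "The primary analysis will be repeated using the PP and safety analysis set". Under Interventions, the control group takes maltodextrin sachets and no creatine. Trial design sets a superiority aim against control. Planned statistical methods calls for treatment differences with confidence intervals and p-values, and for mixed models across groups and time.

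**The concern.** Entry to the FAS depends on a product that only one arm is meant to receive. Read as written, the efficacy population has no comparator, and neither does the PP set taken from it. The superiority question could then not be answered in the set that replaces intention-to-treat for efficacy, or in the first of its two stated repeats. The other repeat uses a set that groups patients by product taken, not by allocation.

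Even if everyone sees that the wording is a slip, someone must decide how to mend it, and the article does not say how. It also states that the person doing the statistical analysis will know the allocation (Randomization and blinding). The primary population should be settled in the text and not left to that person's reading.

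**Working it through.** **Inputs.** There are 15 patients per arm (Interventions; Sample size), allocated 1:1. The article's own figure reproduces: an average of 10 per arm in the cited meta-analysis, raised by 50%, gives 10 × 1.5 = 15 per arm and 15 × 2 = 30 in total. No effect size, standard deviation or power is stated, so there is no power calculation to check.

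**Applying the definitions.** Assume that each patient receives at least one dose of the assigned product and nothing else.

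| Set as written | Entry condition on product | Creatine arm | Control arm |
|---|---|---|---|
| FAS | creatine | 15 | 0 |
| PP (subset of FAS) | creatine, through the FAS | at most 15 | 0 |
| Safety | creatine or placebo | up to 15 | up to 15 |

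The FAS therefore omits 15 of 30 randomised patients (50%), all of them controls.

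**Effect on the planned estimate.** For a difference in means, SE = SD × √(1/n₁ + 1/n₂).

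- FAS as written: √(1/15 + 1/0) is undefined. There is no difference, interval or p-value.
- PP as written: undefined for the same reason.
- FAS with both products named: √(1/15 + 1/15) = √(2/15) ≈ 0.365, so SE ≈ 0.365 SD with full data.

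**Relaxing the assumption.** A control given creatine by mistake would meet the FAS condition and, being analysed as randomised, would count as a control. A few such errors would not make a usable control arm.

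**Which set is primary.** The FAS is assigned to efficacy in general. The PP and safety sets are each assigned to the primary endpoint. The Sensitivity analysis section treats those two as repeats, which implies that the FAS is primary, but no sentence says so.

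**Is it corrected elsewhere?** No other section redefines the FAS. The Background aim and the Outcomes section place the inflammatory and biomarker comparison in all randomised participants. That is a both-arm population for those measurements, but it is not one of the defined analysis sets and is not tied to the primary outcomes as a whole.

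**The case against.** The best counter-argument is that nobody would be misled. An instruction to analyse patients as randomised has no purpose in a one-arm set. The superiority aim, the planned treatment differences and the group-by-time models all need controls. The safety definition in the same section shows what the authors most likely meant. On this view two words were dropped and the intent is plain. That reading is probably right about intent, and it limits the finding. It does not remove it, because the article states a definition, states it wrongly, and corrects it nowhere. This is not detail left to a fuller plan.

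Three stronger readings are tempting and are not supported.

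- *That no between-group comparison is possible in the trial.* This holds for the FAS and PP sets only. The Safety Analysis Set has both arms and is assigned the primary endpoint.
- *That the both-arm set abandons randomisation.* Grouping by product taken departs from grouping by allocation only if someone receives the wrong product. The article gives no rate for that, and dosing takes place in a monitored stroke unit.
- *That the comparison will be biased by dropping undosed patients from the creatine arm alone.* This needs an analyst to mend half the sentence, and creatine-arm patients who never took a sachet. The article gives no figure for either, so this bias is hypothetical and has no size.

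**Conclusion.** The definition is wrong as written and must be corrected, because it governs the main efficacy population. Under the stated wording, with patients treated as assigned, the FAS and PP sets each hold 0 of 15 controls and support no treatment comparison. The only defined set with both arms is the Safety Analysis Set, grouped by product taken.

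A reader might infer that the sponsor plans a one-arm efficacy analysis. The rest of the article points the other way, and the likely explanation is a slip. The count of 15 of 30 measures the literal text and does not predict what will be analysed. The conclusion rests on the planned 15 + 15 and on the article alone. A statistical analysis plan that is not shown may already carry the right wording, but the published definition would still need to agree with it. The planned sample size and the significance level are unaffected.

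**What to change.** 1. Define the FAS as every randomised patient who took one or more doses of either study product, creatine or placebo, analysed in the arm assigned by randomisation.
2. State that the FAS is the primary set for the primary endpoint.
3. Reword the sentence that assigns the primary endpoint to the PP set so that this set gives a sensitivity repeat only.
4. Reword the matching sentence for the Safety Analysis Set so that, beyond safety, it too gives only a sensitivity repeat of the primary analysis.

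With these edits the Sensitivity analysis section can keep its sentence on the PP and safety repeats, and the two sections agree. Removing the primary endpoint from the safety set altogether would create a new conflict with that section unless it were edited as well. Moving to all randomised patients regardless of dosing is a separate design choice that this error does not require.

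The cost is a few sentences in the protocol and, if one exists, the analysis plan, with no added patients or procedures. The change should be made and dated before database lock and before outcomes are compared by arm, since the analyst will not be blinded.

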## Methods

### Trial design

It will be a (randomization 1:1 to the intervention or control groups) double-blind (participants and researchers responsible for administering the supplement and carrying out the protocol assessments), unicenter, parallel-group trial including individuals with ischemic stroke in the acute phase to verify the superiority of the intervention compared to the control group. The duration of the trial for the individual subject will be approximately 90 days, and each subject will attend a maximum of three visits. The protocol was written according to the 2013 Standard Protocol Items: Recommendations for Interventional Trials (SPIRIT) guidelines. A flow diagram of the study is presented in Fig. 1.

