### Sample size

We reviewed a study that analyzed the effects of creatine supplementation in 18 healthy older people, in which 10 patients were allocated to the creatine group and 8 to the control group. The authors observed an improvement in muscle strength, weight, and fat-free mass in the group that received supplementation [22]. In addition, a meta-analysis based on this previous study included approximately 600 patients from 60 studies, with an average of 10 patients in each arm per study [16]. Considering that this is a study on creatine supplementation in patients after stroke, we decided to include 50% more in the convenience sample, with a total of 15 patients in each group.

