### Randomization and blinding

For all subjects, the screening visit and the enrollment visit were performed on the same day. Subjects were randomized 1:1 to the intervention or control groups. The randomization was performed using a cell phone application, which creates a random control and intervention sequence, and was performed in 10 out of 10 participants. No stratification factor was used.

To maintain the blindness of the study, randomization will be performed by a person uninvolved in data collection and data analysis. The participant, the professional responsible for administering the supplements, and the person responsible for conducting the protocol assessments will be blinded to the intervention. The professional in charge of the statistical analysis of the data will not be blinded to the intervention.

Breaking the blinding will be allowed if the participant has a serious adverse effect related to the supplementation, such as an allergic reaction. In this case, the principal investigator will be responsible for breaking the blinding and for informing the hospital’s medical staff about which supplement the participant was consuming.

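### The protocol does not state one clear hierarchy of analysis sets for the primary endpoint, and its literal wording lets a per-protocol result stand as the superiority finding

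*Protocol article*

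**What the plan says.** Under Trial design, the protocol article sets out a parallel-group trial "to verify the superiority of the intervention compared to the control group". The Statistical analysis section then defines three sets and gives each a role:

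- **FAS**, with subjects counted in the group to which they were randomised: "The FAS will be used for efficacy analysis instead of intention-to-treat analysis".
- **PP set**, the part of the FAS with no major deviation, at least good compliance and a derivable primary endpoint: "The PP will be used for the analysis of the primary endpoint".
- **Safety Analysis Set**, with subjects counted by the treatment they actually received: "The Safety Analysis Set will be used for the evaluation of safety endpoints and the primary endpoint".

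The later Sensitivity analysis section adds: "The primary analysis will be repeated using the PP and safety analysis set".

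Randomization and blinding states that the person doing the statistical analysis will know the allocation.

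**The concern.** The primary endpoint is named in the role sentences of two sets, PP and Safety. Neither is the comparison that randomisation protects. PP membership is decided after randomisation by compliance and deviations, and the Safety set is grouped by treatment received. The one set grouped as randomised gets a general efficacy role, and nothing says that it decides the primary endpoint.

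Selection into PP could plausibly be related to outcome in this trial. The Discussion names compliance, level of consciousness, dysphagia and tube feeding as difficulties, and these are likely to go with stroke severity. Data monitoring lists gastrointestinal events related to supplementation, so compliance could also differ between arms.

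At stake is which of up to three versions of each primary result counts. If the as-randomised result is null and the PP result is positive, the literal PP sentence would support reporting the latter as the superiority finding. The choice could be made by an analyst who knows the allocation.

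**Working it through.** **1. The plan's own figure.** Sample size takes about 10 patients per arm from earlier studies and adds half again: "we decided to include 50% more in the convenience sample, with a total of 15 patients in each group". 10 × 1.5 = 15 per group, and 2 × 15 = 30, which reproduces. No effect size, SD, power or expected non-compliance is given.

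**2. The two sections side by side.**

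| Set | Grouping | Role in Statistical analysis | Role in Sensitivity analysis |
|---|---|---|---|
| FAS | as randomised | efficacy, in place of intention-to-treat | not mentioned |
| PP | subset of FAS | primary endpoint, unqualified | repeat of the primary analysis |
| Safety | as treated | safety and primary endpoint | repeat of the primary analysis |

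A repeat presupposes a first analysis on another set. Only three sets are defined and two are repeats, so the first must be the FAS. That is an inference. Nowhere is it stated, and the PP sentence read alone says something different.

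**3. What is at risk if PP decides.** The following is an illustration.

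Inputs from the protocol: 15 per arm; 1:1 allocation ("Subjects were randomized 1:1 to the intervention or control groups"); two-sided 5% ("All statistical tests will be carried out as two-sided and performed on a 5 % significance level").

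Inputs assumed, because the document gives none: the number excluded in each arm, and the correlation ρ between compliance and outcome.

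Model: outcome Y is standard normal in both arms (no effect). Compliance score S = ρY + √(1 − ρ²)·e, with e standard normal. The k patients with the lowest S are dropped from an arm, and the arms are compared by a two-sample t-test over 40,000 replicates.

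The expected shift can be checked by hand. The three lowest of 15 standard normal values have expected values −1.736, −1.248 and −0.948, sum −3.932. Dropping them moves the mean of the remaining 12 by ρ × 3.932/12 = 0.328ρ. Dropping two moves the mean of the remaining 13 by ρ × 2.984/13 = 0.230ρ.

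- 3 v 0: 0.328 × 0.3 / 0.5 / 0.7 = 0.10 / 0.16 / 0.23 SD
- 3 v 2: (0.328 − 0.230) × 0.3 / 0.5 / 0.7 = 0.03 / 0.05 / 0.07 SD
- 3 v 3: 0

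| Excluded, creatine v placebo | Shift (SD) at ρ = 0.3 / 0.5 / 0.7 | False-positive rate |
|---|---|---|
| none, as randomised | 0 | about 5% |
| 3 v 0 | 0.10 / 0.17 / 0.23 | about 6 / 7 / 10% |
| 3 v 2 | 0.03 / 0.05 / 0.07 | about 5 / 6 / 7% |
| 3 v 3 | 0 / 0 / 0 | about 5 / 6 / 7% |

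The table shows simulated values. They match the hand calculation apart from 0.17 against 0.16, which is simulation error. If compliance is unrelated to outcome (ρ = 0), there is no shift and the rate stays at 5%. In the 3 v 3 row the rate can rise without any shift, because cutting off one tail in each arm makes the SD estimate too small.

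**4. The cost of leaving the choice open.** If either the as-randomised or the PP result may be called primary, the 3 v 0 case gives about 6.5% at ρ = 0 and about 7 / 9 / 12% at ρ = 0.3 / 0.5 / 0.7.

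**The case against.** The strongest reply is that the Sensitivity analysis section already supplies the order. It makes PP and Safety repeats, the FAS is the named efficacy set, and the primary outcomes are efficacy outcomes. On that view one section says which sets touch the primary endpoint and the other says in what role, and only the word *supportive* is missing. Most of this stands: FAS first is the most coherent reading.

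It also rules out two stronger inferences.

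- A reader might take the replacement of intention-to-treat to mean that no as-randomised efficacy analysis is planned. The text does not support that, because the set that replaces it is grouped as randomised.
- A reader might conclude that the trial intends to judge superiority on PP or as-treated groups. The Sensitivity analysis section points the other way.

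A further fair objection concerns size. Stroke severity affects both arms of a blinded, 1:1 trial, so exclusions may be nearly balanced, and the bias then becomes small or nil. Larger figures need exclusions confined to one arm.

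What the reply does not remove is that the deciding set must be inferred against an unqualified sentence that gives the primary endpoint to PP. This wording is in the document, so it is more than a detail left to an unseen analysis plan.

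**Conclusion.** The point holds as a fault of hierarchy: the two sections do not together state which set decides the primary endpoint, and the PP sentence read literally permits the wrong one. The documents show no settled plan to rest superiority on PP or as-treated groups.

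The consequence ranges from nothing (compliance unrelated to outcome) to a shift of about 0.23 SD and a false-positive rate near 10% (3 of 15 excluded from the creatine arm only, correlation 0.7). Balanced or nearly balanced exclusions give at most 0.07 SD and about 7%. The number excluded, its split between arms and the correlation are all assumptions. No crossover between arms is reported, so harm from the as-treated grouping is not quantified. The objection to that grouping is one of principle: it suits safety and should not carry an efficacy claim.

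With 30 patients and an unblinded analyst, the deciding set should be fixed in writing before the analysis.

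**What to change.** In Statistical analysis:

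1. State that the primary endpoint is analysed first, and superiority judged only, in randomised patients of both arms, grouped as randomised. Both arms need to be named, because the FAS definition at present mentions a dose of creatine only. That membership wording is a separate matter from the roles discussed here.
2. Change the PP sentence so that the PP set is used for a *supportive sensitivity analysis of the primary endpoint*, in line with the Sensitivity analysis section.
3. Remove the primary endpoint from the Safety Analysis Set sentence.

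In Sensitivity analysis, the as-treated repeat may be dropped. If it is kept, label it supportive only. Deleting it is optional once the lead set is fixed.

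The cost is a few sentences, with no new data and no added analysis. The one downside for the investigators is that the headline result may be slightly less favourable than the PP result.
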